## 2. Materials and Methods

### 2.1. Study Design

The present study protocol describes a non-randomized experimental study, consisting of three groups (1:1 allocation), to assess and compare the effectiveness of two different combined PE (strength + aerobic capacity) for individuals with IDD.

Participants will be allocated to one of the three groups: (i) indoor training group (IG) with sessions carried out in a gym, using weight machines; (ii) outdoor training group (OG) with sessions using low-cost materials; and (iii) control group (CG) with participants continuing to do their normal activities (participation in one of the exercise interventions will not be allowed), based on their interests and availability to be involved with PE programs.

Participants from both intervention groups will participate twice a week, in a 24-week supervised PE program, with sessions lasting 45 min per session. All outcome measures will be collected at three different time moments, at baseline (time 0, baseline assessment, or week 0), at mid-term (time 1, intermidiate assessment, week 12), and at the end of the intervention program time 2, final assessment, week 24). The measurements will be performed after 48 h, after the last workout in both groups, and always in the morning. Figure 1 shows the participant flow for this trial.

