### 2.2. Participants

Adult volunteers, institutionalized in a support institution, located in Leiria, Portugal, recruited by the non-probabilistic convenience method will participate in the program.

In the first step, an individual explanation will be held about the procedures and objectives of the study, as well as the potential benefits, risks, and the time needed for the development of the project.

In a second moment, the participants/family members/tutors will sign a free consent form. Inclusion criteria will be defined: (1) adults with IDD, diagnosed with mild, moderate, or severe IDD; (2) age over 18 years) success in performing movements such as pulling/pushing; (3) capacity to perform the assessments. Exclusion criteria will be defined: (1) individuals who cannot commit themselves for 6 months; (2) individuals with other associated pathologies; (3) contraindications to PE (e.g., high blood pressure); (4) inability to walk unaided; (5) profound IDD; (6) inability to communicate; (7) non-delivery of signed informed consent.

Due to the characteristics of this special population and logistical constraints intrinsic to the development of intervention studies, the sample will consist of the first 21 individuals who agree to participate in the program, aged between 18 and 65. After that, participants will be allocated to one of the three groups. A power analysis (calculated using *G*Power*, version 3.1.9.7 [29] showed that a sample of at least 15 was required to detect a medium effect size (*ES*) of 0.5 (*α* = 0.05, 1 − *β* = 0.95) using a repeated-measures analysis of variance (*ANOVA*), in agreement with some previous studies [30,31]. The effect size of 0.5 was chosen given that this value was verified from studies investigated the effects of exercise on the variables of interest in our study [32,33,34].

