#### 2.4.1. Indoor Training Program

The indoor PE program was carried out in a gym with weight machines. Seven heart rate monitors and seven gym towels will be required. The PE program was divided into four parts. Part I: playful game or shuttle run (5 to 7 min). Part II: aerobic training; Part III: strength training; Part IV: 4 static stretches/cool down. Table 1 shows the training program in detail.

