## 8. Statistical Analysis

In the statistical analysis, descriptive parameters will be used (mean ± standard deviation or percentage) normality and homogeneity will be verified through the *Shapiro*–*Wilk* test and the *Levene* tests, respectively. The existence of significant differences between groups will be analyzed using the *Kruskal*–*Wallis* test and between times using *Wilcoxon* or *Friedman* test. The non-parametric statistic was defined according to the “Central Limit Theorem” [63], in the sense that it will require 30 participants in the sample to have a normal distribution. The magnitudes of the differences will be examined using the *Cohen’s d* effect size [64]. Likewise, associations across studies variables will be verified through the *Spearman* coefficient of bivariate correlations (*r* = 0.10 to 0.29—small; *r* = 0.30 to 0.49—moderate; *r* = 0.50 to 1—strong) [65]. The significance level adopted for all analyses will be *p* < 0.05. For data processing, the computer program *Statistical Package for Social Sciences* (SPSS Science, Chicago, IL, USA), version 28 will be used.

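### Differences are tested with rank methods but sized with mean-based Cohen's d, which at about seven per group is too imprecise to serve as the only named measure of magnitude

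*Protocol article*

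**What the plan says.** All of the following is from the protocol article.

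- Section 8 (Statistical Analysis) plans Kruskal-Wallis between groups and Wilcoxon or Friedman between times. It justifies the rank tests by saying that 30 participants would be needed for a normal distribution.
- The same section continues: "The magnitudes of the differences will be examined using the" Cohen's d. It does not say which d is meant (between-group, paired, pooled or baseline SD) and gives no size bands for it. The only size bands are for Spearman correlations.
- On decisions it says "The significance level adopted for all analyses will be" p < 0.05.
- Section 2.2 (Participants): "the sample will consist of the first 21 individuals who agree to participate in the program". Section 2.1 (Study Design) describes a study "consisting of three groups (1:1 allocation"). Section 2.4.1 (Indoor Training Program) agrees with seven per group: "Seven heart rate monitors and seven gym towels will be required".
- Section 2.2 gives the power statement: "a sample of at least 15 was required to detect a medium effect size" of 0.5, with alpha 0.05 and power 0.95, "using a repeated-measures analysis of variance".
- Sections 5 and 7 remove from the analysis anyone who completes less than 75% of the sessions.

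**The concern.** Two stated choices fit poorly together. The rank tests are chosen because normality is not to be relied on at this size. The magnitude of the same differences is then expressed by a statistic built from means and standard deviations. The test and the effect size rest on different features of the data, so with a skewed outcome or one extreme participant they can point different ways.

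The second problem is precision. At about seven per group, chance alone often produces a between-group d of a size that readers would take seriously. The plan does not say how a sizeable d with p above 0.05 is to be read.

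What is at stake is the trial's main objective (Introduction), to evaluate and compare two programmes, and hypotheses (v) to (viii), which are all between-group. The Abstract makes release of the programmes depend on their showing positive effects. Groups are also formed by participants' own interest and availability, so baseline differences are likely. A d computed at one time point would carry those differences into the stated magnitude.

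**Working it through.** **Inputs.** Total 21 (section 2.2) in three 1:1 groups (section 2.1), so 21/3 = 7 per group. The expected rate of exclusion for low attendance is not given, so I assume 5 to 7 analysed per group. The variant of d is not given, so several are computed.

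**The plan's own figure.** Section 2.2 states a minimum of 15. Take 0.5 as Cohen's f and assume correlation r = 0.5 between repeated measures, sphericity, k = 3 groups and m = 3 times. For the time effect:
- lambda = f² × N × m / (1 − r) = 0.25 × 15 × 3 / 0.5 = 22.5, with df1 = m − 1 = 2 and df2 = (N − k)(m − 1) = 24.
- Power is 0.984 at N = 15 and 0.946 at N = 12, so 15 is the smallest multiple of 3 that reaches 0.95.

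The stated 15 therefore reproduces with 0.5 as f for the within-person time effect. With the same inputs the group-by-time interaction needs 18 (power 0.948 at 15) and the between-group effect needs 45. The 0.5 in section 2.2 is thus an ANOVA input and not a cut-off for d.

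**Between-group d at one time point, no true difference, normal data, equal SDs.** Since d = t × sqrt(2/n),

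P(|d| ≥ 0.5) = 2 × P(t on 2n − 2 df ≥ 0.5 / sqrt(2/n)).

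At n = 7: sqrt(2/7) = 0.5345, and 0.5 / 0.5345 = 0.935 on 12 df.

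| n per group | P(\|d\| ≥ 0.5) | P(\|d\| ≥ 0.8) |
|---|---|---|
| 7 | 36.8% | 16.0% |
| 6 | 40.7% | 19.6% |
| 5 | 45.2% | 24.2% |

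Further results at n = 7:
- Counting one direction only: 18.4%.
- With the small-sample correction to d: 33.7%. The problem is imprecision, and correcting bias does not remove it.
- Simulation (200,000 runs): 37.0% normal, 36.2% uniform, 41.0% lognormal.
- At least one of the three pairwise d values reaches 0.5 in about 64% of simulated normal trials.

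**Interval for d, 7 v 7, by noncentral t.** An observed d of 0.5 has a 95% interval of −0.58 to 1.56. An observed d of 0 has −1.05 to 1.05.

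**How large d must be for p < 0.05.** For a two-sample t test at 7 v 7, |d| must exceed 2.179 × 0.5345 = 1.165. Rank tests differ somewhat, but this shows the wide band of d values that would come with p above 0.05.

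**Other uses of d, n = 7 per group, no true difference, P(|d| ≥ 0.5).**

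| Use | Figure |
|---|---|
| Within-group change over the SD of the differences: 0.5 × sqrt(7) = 1.323 on 6 df | 23.4% |
| Within-group change over the average SD, r = 0.5 / 0.7 / 0.8 / 0.9 | 22% / 12% / 7% / 2% |
| Between-group difference in change over baseline SD, same r | 37% / 25% / 16% / 6% |

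The chance figure therefore depends heavily on which d is meant, and the section leaves that open.

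**The case against.** The strongest case against is that this rests partly on silence. The section is one paragraph of a condensed article, and the sentence on d is not false. Whether estimates carry intervals is commonly left to a full analysis plan. That stands: a reader might infer that d will be reported without an interval, but the article does not say so, and the missing mention alone is no finding.

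Several further inferences also go too far.
- That 37% applies to every comparison. It does not: hypotheses (i) to (iv) concern change over time, where the figure is about 2% to 23%.
- That a d of 0.5 will be labelled medium. Section 8 sets no bands for d, and the phrase "required to detect a medium effect size" belongs to the ANOVA power calculation in section 2.2.
- That non-significant contrasts will be presented as effects. The stated decision rule is p < 0.05, so 36.8% is not an error rate of the plan.
- That a small indoor-outdoor d will be read as similarity. Hypotheses (v) to (viii) look for differences, and no equivalence claim is planned.

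It can also be said that means and standard deviations will be reported, so a reader could work out approximate intervals.

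What survives is a choice that the article does state: mean-based d as the only named magnitude measure, beside rank tests adopted because of the small sample, in groups of about seven.

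**Conclusion.** The point holds as a cheap improvement. It is not an error that invalidates the analysis. The magnitude measure does not match the tests, its variant is undefined, and at this size it says little when standing alone. For a single two-sided between-group comparison at one time point, |d| of 0.5 or more arises by chance in about 37% of cases at 7 v 7, 41% at 6 v 6 and 45% at 5 v 5. An observed d of 0.5 is compatible with roughly −0.6 to 1.6.

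These figures assume normal data, equal SDs, no true difference and equal group sizes. Seven per group follows from the stated 1:1 split, but allocation by preference may not deliver it. The 6 v 6 and 5 v 5 cases are assumed outcomes of the attendance rule. That rule can remove only participants in the two exercise groups, so those cases fit the indoor-outdoor contrast most directly. For within-group change and for differences in change scaled by baseline SD, use the lower ranges in the working.

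**What to change.** In section 8, for indoor-control, outdoor-control and indoor-outdoor, replace d as the main magnitude measure with the difference in change from baseline in the outcome's own units. Give it as a Hodges-Lehmann estimate with a 95% interval. This is the estimate that goes with the pairwise rank-sum test, so it is consistent with the planned non-parametric approach. Working on change also takes some account of baseline differences between self-selected groups, although it does not remove confounding.

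Keep d, if wanted, as a supplement. State its variant (which difference, which SD, and whether small-sample corrected) and give its 95% interval.

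The cost is a few sentences of analysis wording and a little more output. No new data are needed. The drawback is that results will look less certain, which is a fair picture of what about seven per group can show.

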This study has also a multidisciplinary approach, as it is prudent to investigate the combined effects of some independent variables. In addition, we will also examine the hypothetical premise that some objective measures have strong associations with subjective perception measures.

Although there is a clear need to carry out more research on healthy lifestyle interventions for people with more severe levels of IDD (profound IDD), our current intervention is limited to participants with mild to severe IDD, so future studies should take this level of IDD into account

Finally, as with all studies, our study has some limitations, among which we highlight: (1) due to logistical constraints, the groups will not be randomized; (2) it is impossible to control activities outside the PE program, which may affect negatively or positively the variables under study; and (3) the PE program is not adapted to individuals with profound IDD.

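### Crude Spearman correlations in a sample spanning mild to severe IDD can reflect IDD level alone, so a level-adjusted coefficient should be reported beside them and carry the interpretation

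*Protocol article*

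**What the plan says.** Section 8 (Statistical Analysis) states that "associations across studies variables will be verified through the *Spearman* coefficient of bivariate correlations". It grades the coefficients as small (0.10 to 0.29), moderate (0.30 to 0.49) or strong (0.50 to 1), and adds: "The significance level adopted for all analyses will be *p* < 0.05". No covariate or stratum is named, nor the time point or groups over which correlations are computed. The other tests in the section (Kruskal–Wallis, Wilcoxon, Friedman) also take one factor at a time. Section 5 (Procedures) mentions correlations in an open-ended list of analyses without naming a further method.

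On the sample, section 2.2 says that "the sample will consist of the first 21 individuals who agree to participate in the program, aged between 18 and 65". Eligible people are "adults with IDD, diagnosed with mild, moderate, or severe IDD". Section 2.1 forms two trained groups and one untrained group, "based on their interests and availability to be involved with PE programs".

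On the purpose, section 9 (Discussion) says that "it is prudent to investigate the combined effects of some independent variables". It also proposes to examine whether some objective measures are strongly associated with subjective ones.

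**The concern.** IDD level is a likely common cause of several measures that may be correlated. The Introduction says that activity falls as the degree of disability rises, with consequences for fitness, daily living and independence. It also defines IDD by deficits in intellectual and adaptive functioning. A link from level to the cognitive score and the quality-of-life scale is therefore plausible, although the documents do not state one.

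Where two measures both shift with level, a correlation over the whole sample contains the differences between levels, even if the measures are unrelated among people of the same level. At weeks 12 and 24, pooling trained and untrained people can add a second shared shift.

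At stake is the interpretation in the Discussion. A strong link between a fitness measure and quality of life or cognition could be reported when the data show only that people with milder IDD score higher on both.

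**Working it through.** The plan gives no figure for the correlation analysis, so there is none to reproduce.

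**Inputs from the protocol article:** n = 21; three IDD levels; two trained groups and one control group with equal allocation; test at p < 0.05 (two-sided assumed); strong band from 0.50.

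**Assumptions:** the share of each measure's variance explained by level (R²) is 0.1 to 0.5; seven people per level; equal steps between levels; normal residuals; no association within level.

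**Threshold.** The critical coefficient is t/√(n − 2 + t²). With t = 2.093 on 19 df, this is 2.093/√(19 + 4.381) = 0.433. Adjusting for level leaves 21 − 2 − 2 = 17 df.

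**Induced correlation.** Let both measures move by d residual SDs per level, with equal thirds. The between-level variance is 2d²/3, so R² = (2d²/3)/(1 + 2d²/3). The only covariance between the measures is that same 2d²/3, so the induced correlation equals R². Example: d = 1 gives 0.667/1.667 = 0.40.

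**Simulation, IDD level only.** Rates vary by about one percentage point between runs.

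| Level R² | Mean crude rho | Crude p < 0.05 | Crude rho ≥ 0.50 | Adjusted p < 0.05 |
|---|---|---|---|---|
| 0.1 | 0.10 | 7% | 3% | about 5% |
| 0.2 | 0.20 | 14% | 8% | about 5% |
| 0.3 | 0.30 | 27% | 17% | about 5% |
| 0.4 | 0.41 | 49% | 34% | about 5% |
| 0.5 | 0.52 | 75% | 59% | about 5% |

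**Sensitivity to the level mix.** Section 2.2 requires participants to walk unaided, communicate and complete the assessments, so severe cases may be few. Take an assumed split of 12/7/2 and the same steps per level. The variance of the level score (−1, 0, 1) falls from 0.667 to 14/21 − (10/21)² = 0.440. The rows for R² = 0.3, 0.4 and 0.5 then fall from 27%, 49% and 75% to about 15%, 24% and 42%.

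**Training only, after baseline.** With 14 of 21 people shifted by s SD on both measures, the induced correlation is (2s²/9)/(1 + 2s²/9).

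| Shift s (assumed) | Induced correlation | Crude p < 0.05 |
|---|---|---|
| 0.5 SD | 0.05 | 6% |
| 1.0 SD | 0.18 | 13% |
| 1.5 SD | 0.33 | 33% |

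**Power of the adjusted test.** At a within-level correlation of 0.5 on 17 df, simulated power is about 54%.

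**Splitting by group is no way out.** At n = 7 the critical coefficient is 0.754.

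**The case against.** Much of the case on the other side stands.

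- **Secondary role.** The main objective and all eight hypotheses concern change over time and differences between groups. No effectiveness conclusion rests on a correlation.
- **Marginal versus within-level.** The crude Spearman test is valid for the marginal association in a mixed population. When level moves both measures, that association is real. A reader might take the percentages above as inflated type I error. They are not: they show confounding relative to a within-level question, which the plan does not pose.
- **Which measures.** A reader might infer that any two measures will correlate. Only pairs in which both depend on IDD level or training are affected. The Introduction makes the link for activity, fitness and independence, not for cognitive or quality-of-life scores, blood results or heart rate variability.
- **Pooling.** Pooling all groups is the natural reading of section 8, but it is not stated. Training cannot confound baseline values.
- **Combined effects.** A reader might conclude that a stated aim has no analysis. The phrase is a loose remark in the Discussion, with no named variables or outcome, and is not one of the hypotheses. It is enough that bivariate coefficients should not be cited in support of it.
- **Adjusting for group.** Adjusting change scores for group may remove co-change caused by training, which could be the association of interest.

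None of this removes the main difficulty. The Discussion seeks strong objective–subjective associations, and the crude coefficient alone cannot separate such a link from a difference between IDD levels.

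**Conclusion.** The point holds as a limit on what the crude coefficients can be taken to show. For measures that both depend on IDD level, a moderate or strong crude correlation may reflect level alone. The size rests on assumptions that the documents cannot settle. With equal thirds it runs from negligible (7% significant at R² = 0.1) to large (75% at R² = 0.5), and it is clearly smaller if severe IDD is rare. The contribution of training after baseline is close to nominal at a 0.5 SD shift and matters only for larger shifts. The documents support neither a claim that the test is invalid nor a claim that every pair of measures is affected. A level-adjusted coefficient is still a sound and cheap improvement.

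**What to change.** In section 8:

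- Report, on baseline values, a partial Spearman correlation adjusted for IDD level beside the crude coefficient. Base the Discussion's objective–subjective interpretation on the adjusted value.
- If week 12 or week 24 data are correlated, show the result with and without adjustment for group, and state what each version answers.
- Label all correlation analyses exploratory.

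In section 9, do not claim combined effects from bivariate coefficients.

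The cost is wording only, since IDD level and group are already recorded. Adjustment for level uses two degrees of freedom at baseline. Power is modest at about 54%, so a non-significant adjusted coefficient should not be read as showing no association. Adjusting for group as well would take up to two more degrees of freedom, from a sample that the 75% attendance rule may already have reduced.

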Despite the importance of PA and/or PE benefits, this population has high rates of sedentarism and low levels of physical activity engagement [16,17], not meeting the recommendations [18,19], which puts them at greater risk of developing chronic diseases [20] and consequent premature death [21,22]. The risks of physical inactivity in people with disabilities increase when compared to the general population: higher prevalence of hypertension (25 to 41% compared to 29% in the general population); obesity (30.8 to 36.6% compared to 18.2 to 18.5%); and metabolic syndrome (21 to 29.3% compared to 13.5% to 17.9%) [23,24]. In addition, as the degree of disability increases, physical activity levels decrease more significantly [25], affecting their physical fitness, capacity to perform activities of daily living, and independence [26]. To promote their life conditions, people with IDD should be integrated into PA and PE practice, according to recent recommendations [18,19].

One of the possible reasons for these low levels of practice is the existence of barriers that hinder their practice. Among them, we can find factors such as financial cost and lack of adapted PE [27,28]. To reduce the impact of these barriers, it is important to develop PEs. Besides being adapted to the individuals, they must be accessible to any type of context and financial availability, both for the individuals and the support institutions. In addition, the development of these PE may contribute to the reduction in the risk of the onset of metabolic and cardiovascular diseases, which decreases healthcare costs and promotes physical fitness, functionality, and QoL. Therefore, the main objective of the present study is to evaluate and compare the effectiveness of two different 24-week PE programs on levels of physical fitness, general health, dementia/cognitive decline, and QoL in individuals with IDD.

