Therefore, the following hypotheses will be operationalized: (i) individual with IDD increased physical fitness after 12 and/or 24 weeks of PE; (ii) individual with IDD increased general health after 12 and/or 24 weeks of PE; (iii) individual with IDD increased dementia/cognitive decline after 12 and/or 24 weeks of PE; (iv) individual with IDD increased QoL decline after 12 and/or 24 weeks of PE; (v) there was a difference between groups on levels of physical fitness after 12 and/or 24 weeks of PE; (vi) there was a difference between groups on levels of general health after 12 and/or 24 weeks of PE; (vii) there was a difference between groups on levels of dementia/cognitive decline after 12 and/or 24 weeks of PE; and (viii) there was a difference between groups on levels of QoL after 12 and/or 24 weeks of PE.

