### 4.3. Neuromuscular Capacity

Lower limb strength will be assessed using an isokinetic dynamometer (BIODEX Multijoint System 3 Pro, Shirley, NY, USA), which is reliable for the target population [39], through leg flexion and extension, using maximal concentric contractions. Equipment calibration was performed before the evaluation session according to the manufacturer’s instructions (Biodex Medical Systems, Inc., 2000, Shirley, NY, USA). Participants will sit in the equipment chair (chair inclined backward at 85° of hip flexion), according to the manual’s recommendations, and stabilize using crossed belts close to the chest, hip, and thigh of the member to be evaluated, in order to avoid compensation. The axis of rotation of the dynamometer was aligned with the external femoral condyle of the knee. The fixing strip of the pad was adjusted 2 cm above the upper edge of the fibular malleolus. The global range of motion was defined as between 85 and 90°. The individual gravity calibration was corrected before each test in the position of 30 degrees of knee flexion [40]. To familiarize the participants, before starting the test, 3 repetitions were performed for each velocity and action [41]. During the test, participants were instructed to keep their arms crossed with their hands on the opposite shoulder. The computer screen connected to the dynamometer provided consistent visual feedback in real time [42]. The warm-up protocol consists of 5 min of walking at a comfortable intensity. Concentric and eccentric reciprocal muscle actions will be tested considering 3 repetitions for each movement 60°.s^−1^ (1.05 rad/s) and 120°.s^−1^ (3.14 rad/s). A 60 s interval was established between the 3 rep familiarization and the test, as well as between angular velocities [43]. Values will be obtained such as peak torque, Peak TQ/BW, Maximum Repetition Total Work, Coeff of Var., Average Power, Total Work, Acceleration Time, Deceleration Time, ROM, Average Peak TQ, and Agonist/antagonist ratio.

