## 5. Procedures

Intervention study that involves several phases: (a) design of PE programs; (b) promotion of the program (information pamphlets will be distributed to the target people with IDD/guardians/tutors/caregivers about the study procedures and aims); (c) sample recruitment (participants/parents/tutors will sign an informed consent form and all project will be carried out in accordance with the Declaration of Helsinki; (d) division according to their intention to participate in the study: (i) IG/indoor context (using weight machines), (ii) OG (low cost), or (iii) CG (no specific intervention; continue with normal daily activities); (e) initial evaluation of the groups by an evaluator blinded to the group belonging; (f) intermidiate evaluation of the groups by an evaluator blinded to the group belonging; (g) final evaluation of the groups by an evaluator blinded to the group belonging; (h) data analysis: descriptive, comparison between groups and conditions, comparison before and after, correlations, among others (subjects who do not perform at least 75% of the sessions will be excluded from data processing).

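### No primary outcome or time point is named and 0.05 applies to all analyses, so about 3 to 4 false-positive between-group results are expected if neither programme works

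*Protocol article*

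**What the plan says.** The main objective (Introduction) is to evaluate and compare two programmes on "levels of physical fitness, general health, dementia/cognitive decline, and QoL in individuals with IDD". That is four domains, and no variable is singled out in any of them.

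The Introduction lists eight hypotheses. Four concern change within participants, for example "individual with IDD increased physical fitness after 12 and/or 24 weeks of PE". Four concern groups, for example "there was a difference between groups on levels of physical fitness after 12 and/or 24 weeks of PE". None says which variable stands for its domain.

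Section 2.1 states: "All outcome measures will be collected at three different time moments" (weeks 0, 12 and 24). Section 8 states: "The existence of significant differences between groups will be analyzed using the" Kruskal–Wallis test. It assigns Wilcoxon or Friedman tests to differences over time and Spearman coefficients to associations. It closes with "The significance level adopted for all analyses will be" p < 0.05. Section 5 describes the analysis as "data analysis: descriptive, comparison between groups and conditions, comparison before and after, correlations, among others".

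Sections 4.1 to 4.7 list the measures. The isokinetic test alone yields eleven parameters: "Values will be obtained such as peak torque, Peak TQ/BW, Maximum Repetition Total Work" and eight more.

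**The concern.** Three choices are left open together: which variable represents a domain, which follow-up counts, and which comparison decides. The threshold stays at 0.05 throughout. A reader of the results could not tell a planned finding from the most favourable of many tests.

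This matters because the results have a use. The Abstract says both programmes will be made available if they show positive effects, and the article speaks of effectiveness throughout. A few isolated significant results among dozens of tests could be taken as support when they are what chance alone would produce.

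**Working it through.** **1. The plan's own figure.** The article states no familywise error rate. Its one related figure is the required sample of 15 (Section 2.2: effect size 0.5, α = 0.05, power 0.95, repeated-measures ANOVA). Assume the effect size is Cohen's f, with three groups, three measurements and correlation 0.5 between measurements. The within-participant test then has λ = f²·N·m/(1−ρ) = 0.25 × 15 × 3/0.5 = 22.5 and power 0.984. N = 12 gives 0.946, just short, so 15 reproduces. It is the size for one test at 0.05 and makes no allowance for many.

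**2. Number of variables.** Each named measure counted once:

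| Source | Variables |
|---|---|
| 4.1 body mass, BMI, waist | 3 |
| 4.2 body composition (not itemised) | 1 |
| 4.3 isokinetic parameters | 11 |
| 4.3 handgrip, medicine ball throw | 2 |
| 4.4 sit to stand, agility, 6 min walk | 3 |
| 4.5 systolic, diastolic, heart rate, oximetry | 4 |
| 4.5 heart rate variability | 7 |
| 4.6 quality-of-life domains | 8 |
| 4.7 MMSE total | 1 |
| **Total** | **40** |

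Adding one blood analyte and a quality-of-life total gives 42. Using only the quality-of-life total, with one blood analyte, gives 40 − 8 + 1 + 1 = 34. Isokinetic splits by velocity and movement, and separate self and caregiver ratings, are left out.

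**3. Expected false positives.** This is variables × 2 follow-ups × 0.05, whatever the correlation:
- 34 variables: 68 × 0.05 = 3.4
- 40 variables: 80 × 0.05 = 4.0
- 42 variables: 84 × 0.05 = 4.2

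**4. Chance of at least one, 80 between-group tests.** Independent: 1 − 0.95⁸⁰ = 0.983. With equally correlated normal test statistics, by numerical integration: 0.909 at correlation 0.3, 0.729 at 0.5 and 0.468 at 0.7. With 34 variables (68 tests), the four values are 0.969, 0.877, 0.692 and 0.446.

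**5. Adding the within-group tests.** The planned tests were simulated with no effect, 7 per group and 40 variables: Kruskal–Wallis at weeks 12 and 24, plus Friedman in each exercise group. At least one p < 0.05 occurred in 0.98 of trials at between-variable correlation 0.5 and in 0.91 at 0.7. In a block structure (eight blocks, 0.7 within and 0.2 across), Kruskal–Wallis alone gave 0.87, and 0.99 with Friedman added.

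**6. One variable at two times.** Two normal tests at 0.05 give an error of 0.091, 0.084 and 0.078 at between-time correlation 0.5, 0.7 and 0.8. Simulated Kruskal–Wallis tests with 7 per group give 0.084, 0.078 and 0.074. Hence about 7 to 9% instead of 5%.

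**7. Friedman.** One Friedman test covers all three times at once. Its simulated size is 0.051, 0.047 and 0.053 for 7, 14 and 21 participants, so it does not carry this inflation.

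**The case against.** The strongest objection is that independence is implausible. Several torque and work parameters come from the same contractions, several heart rate variability indices from one recording, and BMI contains body mass. A reader might infer that a significant finding is near certain even if neither programme works. For the between-group tests this holds only near independence; at common correlation 0.7 the chance is about one half. This stands, so the probability is given as a range. The expected count of 3 to 4 does not depend on correlation.

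A reader might also infer that none of the eight hypotheses is held at 5%. That goes too far. Cognition has one named total score, and a single Friedman test on it holds about 5%, although testing each exercise group separately would raise that.

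The article does not say that one significant test confirms a hypothesis, nor that every value obtained will be tested. It gives no decision rule at all, and that gap is the point. Adjusted p-values could be compared with 0.05, and an unseen analysis plan might specify them. But the article itself sets the level for all analyses and words the hypotheses to be met at either time.

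The count of variables is also soft: blood and body-composition variables are not itemised, and whether quality of life is analysed by domain or total is not stated. The range 34 to 42 allows for the quality-of-life choice.

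Finally, the Discussion calls the work a pilot. It does not label the tests exploratory, and it claims to compare effectiveness.

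**Conclusion.** The point holds in a limited form. With no primary outcome or time, 0.05 for all analyses and hypotheses met at either follow-up, the between-group tests alone produce about 3 to 4 expected false positives when neither programme works. For 80 tests the chance of at least one runs from 0.98 (independent) to about 0.5 (common correlation 0.7), and it rises once within-group tests are counted. The between-group error for a single variable is about 7 to 9%.

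These figures rest on the variable count above, on all counted measures being tested at both follow-ups, on no adjustment being applied, and on assumed correlations.

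A reader might go on to infer that low power makes most significant results chance or exaggerated. The documents do not support this: the share of true effects is unknown, and the sample-size calculation, on its own assumed effect, does not show low power.

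**What to change.** Before any analysis:

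- Name one primary outcome measured in all three groups, for example 6 min walk distance or 30 s sit to stand. The three-repetition maximum is unsuitable because only the indoor group takes it (Section 4.3).
- Fix week 24 and one between-group test at 0.05, for example the three-group comparison of change from baseline, with pairwise comparisons only if it is significant.
- Name one key measure for each other domain: a general-health measure of the sponsor's choice (such as resting systolic pressure), MMSE total and Personal Outcomes Scale total. Test these three with Holm (smallest p against 0.05/3 = 0.0167) only if the primary is significant. Alternatively, put all four in one Holm family (smallest p against 0.05/4 = 0.0125).
- Reword the hypotheses to refer to week 24 only.
- Report all other variables, week 12 and the correlations as exploratory, with estimates and 95% confidence intervals and no significance claims. Within-group tests over time either join the Holm family or are treated the same way.

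This takes a few sentences and no extra data. The price is that fewer results can be called significant. It does not remove bias from participants choosing their group by interest and availability (Sections 2.1 and 2.5).
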